## Methods/design

This will be a prospective, randomised, parallel, open-label, single-centre, feasibility study with allocation concealment and blinded assessors. The study has been designed in accordance with the Standard Protocol Items: Recommendations for Interventional Trials (SPIRIT 2013) [48] and the Consolidated Standards for Reporting of Trials CONSORT guidelines [49] (Fig. 1, study flow diagram). The study will be undertaken at the university-affiliated tertiary care hospital - the Royal Adelaide Hospital, Adelaide, Australia.

**Fig. 1 Fig1:**
[figure not shown]
Study flow diagram. Flow diagram of patient recruitment and study conduct

### Study participants

Participants will be recruited from those patients being discharged from the ICU at the Royal Adelaide Hospital over a 12 to 18-month period (between February 2016 and August 2017). Patients will be approached once they become eligible and liberated from mechanical ventilation. Inclusion and exclusion criteria are described in Table 1. Type 2 diabetes will be defined according to national guidelines [50, 51]. Patient consent will be obtained by one of the investigators.

**Table 1 Tab1:** Inclusion and exclusion criteria

Inclusion criteria	
Established pre-admission diagnosis of type 2 diabetes mellitus	
Discharged from ICU after ≥5 days of ICU care	
Exclusion criteria	
Distance from hospital to home >50 km	
Age >85 years	
Major psychiatric illness	
Anticipated to die within 6 months of ICU discharge	
Pregnancy	

### Baseline data collection

Baseline data, including patient demographics, admission diagnosis, ICU length of stay, severity of illness according to acute physiology, age and chronic health evaluation (APACHE) II and sequential organ failure assessment (SOFA) scoring systems [52, 53], kidney injury during ICU admission utilising the RIFLE criteria [54] and serum urea and creatinine levels, employment status, degree of frailty before hospital admission as measured by the Canadian Study on Health and Aging Clinical Frailty Scale [55], diabetes duration and treatment, and glycated haemoglobin level will be recorded. Information regarding consent processes will be collected.

### Randomisation

All patients who provide consent for participation and fulfil the inclusion criteria will undergo simple randomisation to either the intervention or control group with a 1:1 allocation by a computerised random number generator; https://www.randomizer.org. The randomisation sequence will be generated, and study arm allocation will be assigned by a designated research coordinator who is not involved in the study. The randomisation sequence will be concealed from the staff enrolling and consenting participants to prevent selection bias. The randomisation sequence will be protected by an electronic password known only to the designated research coordinator.

### Intervention group

Patients in the intervention group will be asked to record their blood glucose level after discharge using a provided form. Patients receiving oral hypoglycaemic agents alone will be asked to record their daily fasting blood glucose level, followed by levels twice daily in the week prior to attendance at the follow-up clinic. Patients receiving subcutaneous insulin will be asked to record their blood glucose level at least twice daily after discharge until review at the clinic. When feasible, patients will undergo continuous glucose monitoring in the week prior to clinic attendance.

All patients in the intervention group will receive a telephone call 2 weeks after hospital discharge as a reminder of the upcoming clinic appointment. During this phone call, inquiries about hypoglycaemic (blood glucose level <4 mmol/L) or hyperglycaemic (blood glucose level >13 mmol/L) blood concentrations will be made. If necessary, changes in treatment will be instituted by the study diabetologist and recorded for each patient. Patients will also undergo blood testing for glycated haemoglobin, complete blood count, electrolytes, renal and liver function, calcium profile, vitamin D level, lipid profile, vitamin B_12_ level, folate level, iron studies, thyroid function, gonadotropin levels and testosterone level (male patients) during the week prior to the clinic attendance and prior to the 6-month assessment. Fructosamine will be measured as an additional marker of glycaemic control prior to the clinic attendance [56].

Attendance at the shared care follow-up clinic will occur 1 month after hospital discharge (±14 days). Patients will be assessed by both an intensivist and a diabetologist at the clinic as outlined in Table 2.

**Table 2 Tab2:** Evaluation at the ICU follow-up clinic

Diabetologist assessment	Intensivist assessment
Anthropometric measurements	Semi-structured interview to assess for long-term complications of ICU admission
History of diabetes and treatment	Discussion of ICU experience
Review of blood glucose levels and diabetes medications	Assessment of mobility
Assessment of cardiovascular risk	Screen for anxiety and depression
• Blood pressure check and titration of antihypertensives	Assessment of employment status and frailty
• Lipids	Quality of life questionnaire
• Indication for aspirin	Review of patient healthcare utilisation diary
Diabetes complications screen	Referral to other specialists or services as required
• Nephropathy	
• Peripheral neuropathy	
• Cardiovascular autonomic neuropathy	
• Retinopathy	
• Macrovascular complications	
• Referral to ophthalmologist or podiatrist as appropriate	

Evaluation will include measurement of vital signs and basic anthropometric data; history-taking regarding diabetes and its treatment; review of blood glucose levels and continuous glucose monitoring data; adjustment of oral hypoglycaemic agents or insulin dosing as required; overall medication review; and cardiovascular risk assessment. Glycaemic targets will be tailored for each patient taking into consideration diabetes duration, diabetes medication regimen, the presence of cardiovascular disease, comorbidities and problems with hypoglycaemia [57]. Blood pressure, lipid profile and requirement for aspirin will be assessed and treatment instituted based upon published guidelines for patients with diabetes [58]. Patients will also undergo evaluation for complications of diabetes including nephropathy (serum urea and creatinine, spot and, if required 24-h, urine albumin) [59]; distal peripheral sensorimotor neuropathy [60]; cardiovascular autonomic neuropathy using validated cardiovascular autonomic reflex tests [61, 62] performed by ANX 3.0 Autonomic Nervous System monitoring technology (The ANSAR Group, Philadelphia, USA) and macrovascular complications (ischaemic stroke, myocardial ischaemia, peripheral vascular disease) when appropriate.

Patients and, if necessary, their carers will be interviewed and systematically asked about any problems which have developed since ICU admission including pain, airway obstruction, symptoms of autonomic neuropathy, sexual dysfunction, concerns about cosmesis and any impairments of vision, hearing, taste, swallowing, appetite, cognition or communication as recommended in international clinical guidelines [47]. Such systematic interviewing has been used previously in the ICU follow-up clinic setting [6]. Patients will be screened for mobility limitations using the Modified Rivermead Mobility Index [63], and patients of concern will be referred to the physiotherapy department of the hospital. The ICU experience will be discussed, and patients will be screened for psychological distress using the Hospital Anxiety and Depression Scale (HADS) [64]. Patients with a high HADS score will be referred to the hospital’s psychology clinic if eligible, or otherwise to their general practitioner for formation of a Medicare-funded Mental Health Treatment Plan. Both the Modified Rivermead Mobility Index and the HADS have been previously used in studies of ICU survivors [45, 46].

Following the above assessments and discussion between the intensivist and diabetologist, patients may require referral to additional healthcare professionals, including diabetes nurse educators, podiatrists, ophthalmologists, dietitians and other medical or surgical specialists. All referrals will follow standard hospital pathways. If deemed required, an additional clinic visit will be offered to patients in the intervention group prior to the assessment at 6 months. A written summary of the outcomes from the clinic visit/s will be provided to each patient’s general practitioner.

### Control group

Patients in the control group will have usual care in accordance with standard clinical practice, so that follow-up after ICU will be at the discretion of the primary inpatient hospital team and the patient’s general practitioner.

Patients will undergo blood testing for glycated haemoglobin, complete blood count, electrolytes, renal and liver function, calcium profile, vitamin D level, lipid profile, vitamin B_12_ level, folate level, iron studies, thyroid function, gonadotropin levels and testosterone level (male patients) during the week prior to the 6-month assessment.

### Outcome measures

All patients in the intervention and control groups will be contacted by mail and telephone and invited back at 6 months after hospital discharge for assessment. Patients will be assessed by two blinded assessors (an intensivist and a diabetologist) who were not present at the follow-up clinic. Before undergoing this assessment, patients in the intervention group will be instructed not to refer to their prior attendance at the follow-up clinic so that the assessors remain blinded.

#### Primary outcome

The primary outcomes of this study are the recruitment rate over the 12 to 18-month recruitment period of the study and the rate of retention of enrolled patients for six months. The number of eligible patients during the recruitment period will be recorded, along with reasons for refusal of consent. Success of the feasibility study will be determined if ≥50 % of all eligible patients are recruited and complete six-month data is obtained in ≥80 % of these patients.

#### Secondary outcomes

A number of secondary outcomes will be collected for descriptive purposes. Anthropometric data based on Australian longitudinal studies of ambulant patients with type 2 diabetes will be collected [65]. Glycated haemoglobin will be quantified as a marker of glycaemic control using high-performance liquid chromatography [56]. The capacity of patients using insulin or sulphonylureas to detect hypoglycaemia and symptoms of hypoglycaemia will be assessed using a validated questionnaire (the Clarke score) [66]. Patients will be assessed for the presence of distal symmetrical peripheral neuropathy with the Michigan Neuropathy Screening Instrument, a simple non-invasive and valid measure comparable to the ‘gold standard’ of an examination performed by a neurologist combined with electrophysiology examinations [60]. Testing for cardiovascular autonomic neuropathy will be performed using the ANX 3.0 Autonomic Nervous System monitoring technology (The ANSAR Group, Philadelphia, USA) according to the latest consensus guidelines for the diagnosis of autonomic dysfunction and patients categorised as having autonomic dysfunction if two or more tests are outside the age-adjusted reference range [61, 62]. The sympathetic response will be evaluated following the Valsalva manoeuvre for those unable to perform orthostatic provocation [61]. Patients will be screened for nephropathy with serum urea and creatinine and spot urine testing. If two spot urine samples are suggestive of macroalbuminuria, urine will be collected for 24 h and analysed for protein [59].

HRQoL scores will be measured with the EuroQol EQ-5D-5L and the short form-36 (SF-36) survey [67, 68]. Both instruments are valid and sensitive, have been used in studies of ICU survivors, and demonstrate good completion rates by telephone or mail if necessary [3, 6, 45, 69, 70]. Rates of HRQoL questionnaire completion will be reported. HRQoL scores have been used as the primary outcome in the largest study of ICU follow-up clinics to date [45] and, if high HRQoL questionnaire completion rates are demonstrated in this feasibility study, the general health component of the SF-36 will serve as the primary outcome of a subsequent larger study.

Additional secondary outcomes related to functioning in the community and healthcare resource use will also be collected. These outcomes may also serve as secondary outcomes in a subsequent larger study. The degree of frailty will be assessed using the Canadian Study on Health and Aging Clinical Frailty Scale [55], a validated tool which has previously been used in the Australian ICU setting [71] and may predict outcomes in critically ill patients [72]. Employment status will be recorded. Healthcare utilisation data will be collected prospectively using patient monthly diaries and corroborated with hospital inpatient and outpatient clinical records and self-reports at scheduled study visits. This validated approach provides patient-specific and activity-based resource-use data after hospital discharge [6, 73]. We will specifically collect data about hospital and ICU readmissions; inpatient and outpatient rehabilitation service utilisation; hospital emergency room and outpatient clinic visits; general practitioner and specialist visits; diagnostic tests; home care services and provision of specialised medical equipment. If required when an inpatient admission occurs, we will obtain (with the patient’s consent) the medical record to confirm the dates of admission, reason for admission and types of treatment received.

The outcome measures will be taken 6 months after hospital discharge by blinded assessors. EuroQol EQ-5D-5L scores, employment status and healthcare utilisation data will also be collected during the follow-up clinic visit 1 month after hospital discharge in the intervention group. Patients failing to attend the assessment visit will be contacted by telephone and/or mail, provided with the relevant questionnaires for completion, and asked to make their diaries available to the research team. Reasons for non-attendance at the clinic and the assessment appointment will be recorded.

The resources necessary for the study will also be quantified. This will include the hours per week a research coordinator is employed to assist with screening, recruitment and data management. The cost of employing the research coordinator will be calculated. The time required for the diabetologist and intensivist to assess each patient at the follow-up clinic, as well during the 6-month outcome assessment visit, will be recorded. The cost of all blood tests requested will be quantified. The amount of any honoraria paid to participants to cover transport costs and the participants’ time will also be collected.

### Analysis plan

For the main SWEET-AS study, the target sample will be 206 study participants. This is based on previous local mean values for the physical component summary score of the SF-36 of 41 with standard deviation of 10 [74], setting a clinically meaningful difference of 5, and allowing for 20 % drop outs, which will provide 90 % power (alpha 0.05) using two-tailed testing.

Based upon data from the Royal Adelaide Hospital [7], it is anticipated that there will be 80 eligible patients over the 12-month feasibility study period. The study will, accordingly, be deemed successful if at least 40 patients are recruited (50 % of all eligible patients) and complete 6-month data is obtained for at least 32 patients (80 % retention rate). If participant recruitment is significantly less than this, the study can be extended for a further 6–12 months.

Baseline comparison of patient demographics, severity of illness scores and ICU length of stay will be presented. Other scientific outcomes measured at 6 months after ICU discharge (glycated haemoglobin, HRQoL scores, Michigan neuropathy score, Clarke hypoglycaemia score, presence of cardiovascular autonomic neuropathy and nephropathy) will be reported for the entire cohort as a whole, allowing the participant data to be included in the main larger study. Reasons for missing data will be reported. Healthcare utilisation data will be reported descriptively, including the number of hospital and ICU readmissions, emergency room visits, general practitioner and specialist visits, and attendances at inpatient or outpatient rehabilitation services.

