### Study objectives

The objective of this study is to establish the feasibility of conducting a definitive trial to evaluate the benefits of a shared care intensivist and diabetologist-led clinic for ICU survivors with pre-existing type 2 diabetes. Feasibility will be established by quantifying:(i)Study processes—the rate of recruitment of study participants using the proposed inclusion and exclusion criteria over 12–18 months and the rate of retention of the participants for a 6-month period(ii)Resources required—an accurate estimate of time and budget requirements(iii)Scientific effects—preliminary data relating to the potential effects of critical illness on chronic glucose metabolism, the prevalence of complications and the impact on healthcare utilisation and quality of life in intensive care survivors with type 2 diabetes. These data are necessary for confirmation of our initial calculation of sample size for the major study.

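### Glycated haemoglobin is reported only as a pooled 6-month value, so it cannot speak to change after critical illness, although a baseline value is already recorded

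*Protocol article*

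**What the plan says.** The Study objectives section, item (iii), lists among its scientific effects "preliminary data relating to the potential effects of critical illness on chronic glucose metabolism". The Discussion paragraph of the Abstract repeats this as something the study will deliver.

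Under Baseline data collection the article states that "diabetes duration and treatment, and glycated haemoglobin level will be recorded". It also collects the "degree of frailty before hospital admission as measured by the Canadian Study on Health and Aging Clinical Frailty Scale", and "serum urea and creatinine levels, employment status".

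Secondary outcomes then measures the same quantities at 6 months: "Glycated haemoglobin will be quantified as a marker of glycaemic control using high-performance liquid chromatography"; "The degree of frailty will be assessed using the Canadian Study on Health and Aging Clinical Frailty Scale"; "Employment status will be recorded". Serum urea and creatinine are repeated as part of the nephropathy screen.

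The Analysis plan names demographics, severity scores and ICU length of stay for the baseline presentation. It then lists "Other scientific outcomes measured at 6 months after ICU discharge", with glycated haemoglobin first, to be reported for both arms together so that participants can enter the later main study. Frailty and employment are not in that reporting list. Change from baseline is not mentioned anywhere in the article.

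**The concern.** An effect of an illness on a chronic state is a departure from some reference level. The trial has no comparison group without an ICU stay, so the only reference available is the patient's own earlier value. The Analysis plan reports glycated haemoglobin without that value.

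All participants had type 2 diabetes before admission. A raised pooled mean at 6 months is therefore what one would see if control had been poor for years, and equally if it had worsened after the ICU stay. The stated summary cannot tell these apart, so the glucose part of objective (iii) would be left without usable data even though the study collects them.

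**Working it through.** **1. Which outcomes have a pair of values.** Setting Baseline data collection beside Secondary outcomes and the Analysis plan:

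| Variable | Baseline value | 6-month value | Reporting stated in Analysis plan |
|---|---|---|---|
| Glycated haemoglobin | Yes, time of sampling not stated | Yes | 6-month value, pooled |
| Clinical Frailty Scale | Yes, explicitly before admission | Yes, same scale | Not listed |
| Employment status | Yes | Yes | Not listed |
| Serum urea and creatinine | Yes, listed with kidney injury during the ICU stay | Yes | Presence of nephropathy only |
| SF-36, EQ-5D-5L, Michigan score, Clarke score, autonomic neuropathy, albuminuria | None listed | Yes | 6-month values, pooled (HRQoL, Michigan and Clarke scores, autonomic neuropathy, nephropathy) |

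Within-patient change is possible for the first four rows only. Only the frailty score is explicitly a pre-illness value.

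**2. Number of pairs.** The Analysis plan expects 80 eligible patients, with success at 50 % recruitment and 80 % retention: 80 × 0.5 = 40 recruited and 40 × 0.8 = 32 with complete data. Both figures reproduce. The 32 is a minimum for success, not a forecast.

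**3. Precision of the summary as planned.** In units of the outcome SD, the 95 % half-width for a mean is t(0.975, n − 1)/√n. With n = 32 this is 0.361 SD. It describes a level, not a change.

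**4. Precision of mean within-patient change.** Assuming equal SDs at both times and correlation r, the half-width is 0.361 × √(2(1 − r)):

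- r = 0.3: 0.361 × 1.183 = 0.43 SD
- r = 0.5: 0.361 × 1.000 = 0.36 SD
- r = 0.6: 0.361 × 0.894 = 0.32 SD
- r = 0.7: 0.361 × 0.775 = 0.28 SD

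If all 40 gave pairs, the first factor would be 0.320 and the half-width would run from 0.38 SD (r = 0.3) to 0.25 SD (r = 0.7). The article gives no correlation and no SD for glycated haemoglobin, so r is an assumption and the result stays in SD units. From r = 0.5 upward, change is estimated at least as precisely as the planned 6-month mean. This calculation suits glycated haemoglobin. It does not suit the frailty scale, which is ordinal, or employment, which is categorical.

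**5. Compatibility with the roll-over.** The arms are pooled so that the data can be used again in the main study. Change pooled over arms contains no between-arm contrast, so it meets the same constraint.

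**The case against.** The strongest reply is that this is an omission a fuller plan may already fill. The article does not forbid a change analysis, and change summaries are often left to a statistical analysis plan. A reader might infer that the sponsor has excluded such an analysis; the text does not support that. What remains is that the article has its own Analysis plan, which fixes the time point, the variables and the pooling for these outcomes, and the summary so fixed does not match the glucose part of the objective.

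A reader might also infer that the study cannot inform objective (iii) at all. That goes too far. Prevalence of complications, healthcare use and quality of life can be described from the planned data. The same objective says the data serve to confirm the main-study sample size. That calculation rests on the SF-36 physical component score, which has no listed baseline, so the change proposed here adds nothing to it.

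Third, pooled change does not identify an effect of critical illness. There is no comparator without an ICU stay, and about half the cohort is allocated to a clinic where a diabetologist may adjust glucose-lowering treatment. Change therefore mixes illness, intervention and natural course. This stands in full and governs how the result must be labelled.

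Fourth, urea and creatinine are listed beside kidney injury during the ICU stay. If they were taken during acute illness, their change to 6 months could show recovery from acute injury. This also stands, and it removes them from the proposal.

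Finally, neither success criterion depends on these outcomes, which the article collects for description. That limits the weight of the point but does not remove it.

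**Conclusion.** The point holds in a limited form. For glycated haemoglobin, the reporting in the Analysis plan does not serve the glucose part of objective (iii), and the data that would serve it better are already collected. The same data would also give a use to the paired frailty and employment records, which currently have no stated analysis; objective (iii) does not name function, so this is an addition and not a mismatch.

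The gain is a descriptive estimate of change with a half-width of about 0.43 to 0.28 SD. This rests on 32 pairs, equal SDs at both times and assumed correlations of 0.3 to 0.7. It is not an estimate of a causal effect of critical illness. Recruitment, retention and the main-study sample size are untouched.

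**What to change.** In the Analysis plan:

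- Add glycated haemoglobin to the baseline presentation, and report its within-patient change to 6 months with a 95 % confidence interval, pooled over arms, beside the 6-month value.
- Report the shift in Clinical Frailty Scale from before admission to 6 months, and a simple before/after table for employment status, also pooled.
- State when the baseline glycated haemoglobin was taken. State also from which discharge the 6 months run: the Analysis plan counts from ICU discharge, while Secondary outcomes counts from hospital discharge, and the two should be reconciled.
- Label the results as descriptive change in a cohort of which about half were allocated to the clinic. Allocation is the right word, since the article itself provides for non-attendance.
- Do not present change in urea or creatinine as an effect of critical illness.

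The cost is a few summary rows from data already held, with no new measurement and no arm contrast revealed. The one real downside is that a before/after figure invites over-reading, which the label is there to limit.
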